#### Secondary outcomes analyses

Secondary endpoints include outcomes spanning sleep, circadian rhythms, mood, cognition, frailty, physical activity, body composition, vitamin D status, and feasibility-related measures, assessed at BL, MP, EP, and FU, depending on the measure.

Quantitative differences across assessment time points will be examined using GLMMs or linear mixed-effects models, depending on the distributional properties of each outcome. Models will include group, assessment block, and group-by-assessment block interaction as fixed effects, with participant included as a random effect to account for repeated measures.

Statistical significance will be assessed using a two-sided alpha level of 0.05. p-values will be calculated using likelihood ratio tests comparing models with and without the parameter of interest. Unstandardised effect sizes (beta coefficients) will be reported. A false discovery rate correction will be applied within each branch of secondary outcome analyses, based on the number of models or tests performed within that branch.

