### Study design

The LightSPAN trial is a randomised, double-blind, parallel-group, placebo-controlled trial conducted among community-dwelling older adults in Singapore. The trial is conducted at Lions Befrienders Active Ageing Centres across Singapore, which serve as community hubs for older adults.

Following eligibility screening and informed consent, participants undergo a 4-week baseline observation period during which habitual light exposure, sleep, and activity patterns are monitored using wearable devices. Participants are then randomised in a 1:1 ratio to either the intervention arm, which receives the LightUP app with active behaviour change features, or the control arm, which receives a placebo version of the app without behavioural components. The intervention period lasts 12 weeks and is followed by a 12-week post-intervention follow-up period, including a 2-week monitoring phase. Study staff conducting outcome assessments are blinded to group allocation throughout the study.

All assessments and app-based interventions are coordinated by TUMCREATE. Participants are expected to attend assessments at the respective Active Ageing Centres, while the intervention itself is delivered in participants’ home environments using smartphones and wearable devices. Participating Active Ageing Centres provide accessible facilities for participant recruitment and assessment. Personnel involved in delivering the intervention and conducting assessments are trained research staff with specific expertise in cognitive, mood, frailty, and physical performance testing, ensuring consistency and quality in data collection.

The trial design therefore allows for evaluation of both short-term (during intervention) and sustained (post-intervention) effects on light exposure, circadian rhythms, sleep, mood, cognition, frailty, physical activity and vitamin D status. This protocol adheres to the Standard Protocol Items: Recommendations for Interventional Trials (SPIRIT) 2025 guidelines to ensure complete and transparent reporting [18].

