#### Time points for analysis

Primary and secondary outcomes will be analysed at baseline (week 4), mid-intervention (week 10), end of intervention (week 16) and follow-up (week 28), depending on the measure. Continuous monitoring outcomes (e.g. light exposure, actigraphy, mood diaries) will be aggregated into daily or weekly metrics as appropriate.

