~ 9 min/day increase above 1000 lx melanopic EDI~ 20 min/day increase above 250 lx melanopic EDI~ 30 min/day reduction below 10 lx melanopic EDI in the evening

However, to account for:

Additional outcome domains such as sleep, mood and cognitive function, which may show greater variability or require larger sample sizes to detect meaningful effectsConsidering the intensive nature of the trial and to effectively account for potential dropouts, an expected attrition rate of 25–30%, which is typical in studies involving older adultsThe need for more robust, generalizable results across a wider population

We plan to recruit a total of 90 participants (45 per group). This allows for approximately 63–68 participants to complete the study, corresponding to 31–34 participants per group, even after accounting for attrition. The recruitment strategy is guided by findings from similar mHealth interventions involving older adults, where dropout rates tend to be higher due to factors such as technology challenges, health status and varying levels of digital literacy. Studies in this demographic [35, 36] have demonstrated that over-recruiting by approximately 25–30% is a best practice to ensure adequate sample sizes for meaningful data analysis. By aiming to recruit at least 90 participants, we align with research standards that suggest this number is sufficient for exploratory analysis of the intervention’s effectiveness and feasibility.

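### Continuous secondary outcomes measured once per visit: a participant random intercept assumes equal correlation over 6- to 24-week gaps, so week-10 and week-28 change coefficients would be miscalibrated if correlation falls with time

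*Protocol article*

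**What the plan says.** The protocol's Secondary outcomes analyses section sets the fixed effects: "Models will include group, assessment block, and group-by-assessment block interaction as fixed effects". It then completes the model "with participant included as a random effect to account for repeated measures". It names no block-level random effect, residual correlation structure or robust standard error. The Primary outcome analysis section, by contrast, writes out a by-participant assessment-block term.

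On inference, the secondary section fixes a two-sided 5% level. Of the test it says "p-values will be calculated using likelihood ratio tests comparing models with and without the parameter of interest", and on the effect measure it adds "Unstandardised effect sizes (beta coefficients) will be reported". A false discovery rate correction follows within each branch of outcomes.

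The Time points for analysis section places the assessments at "baseline (week 4), mid-intervention (week 10), end of intervention (week 16) and follow-up (week 28), depending on the measure". The Study design section says that the design allows "evaluation of both short-term (during intervention) and sustained (post-intervention) effects". A separate statistical analysis plan is announced but is not available here.

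**The concern.** With one value per visit, a random intercept and a common residual imply a single correlation for every pair of visits. With complete data they therefore imply a single variance for every change from baseline. Those changes span 6, 12 and 24 weeks. For quantities that drift within a person, such as weight, vitamin D, sleep or mood, one would expect measurements 24 weeks apart to agree less well than measurements 6 weeks apart. The week-28 change would then vary more than the week-10 change, while the model gives both the same averaged variance.

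With baseline as the reference block, the week-28 group-by-block coefficient is the natural measure of a sustained effect, and the week-10 coefficient of an early one. If those coefficients are tested or given intervals one at a time, the first would be tested too liberally and the second too conservatively, with a loss of power.

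**Working it through.** **Inputs from the protocol.** Visits at weeks 4, 10, 16 and 28. Gaps from baseline are therefore 6, 12 and 24 weeks, and the six pairwise gaps are 6, 12, 24, 6, 18 and 12 weeks. Two-sided alpha is 0.05. There are 90 participants, 45 per group, with 25–30% attrition expected. The stated number of completers reproduces: 90 × 0.70 = 63 and 90 × 0.75 = 67.5. The protocol gives no figure for the precision of any secondary outcome.

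**Assumed, because the documents do not say.** Correlations between visits, equal variance σ² at every visit, normal data, baseline as reference block, and complete data in the formulas.

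**Formulas.** With n per arm and r the correlation between baseline and the visit in question:
- True variance of the between-group difference in change = (4/n) σ² (1 − r).
- Variance that the random-intercept model assigns = (4/n) σ² (1 − r̄), where r̄ is the mean correlation over the six visit pairs.
- Ratio of model SE to true SE: k = √[(1 − r̄)/(1 − r)].
- True size of a nominal 5% test of that coefficient = 2[1 − Φ(1.96 k)].

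**Worked example.** Let correlation fall linearly from 0.80 at 6 weeks to 0.60 at 24 weeks, so that it is 0.733 at 12 and 0.667 at 18. Then r̄ = (0.80 + 0.733 + 0.60 + 0.80 + 0.667 + 0.733)/6 = 0.722, and 2(1 − r̄) = 0.556. The true values 2(1 − r) are 0.40 at week 10, 0.533 at week 16 and 0.80 at week 28. At week 28, k = √(0.556/0.80) = 0.833 and the size is 10.2%. At week 10, k = √(0.556/0.40) = 1.18 and the size is 2.1%. Week 16 gives 4.6%.

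**Range.**

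| Assumed correlation at 6 / 12 / 24 weeks | Size at week 10 | Size at week 28 |
|---|---|---|
| Constant 0.60 | 5.0% | 5.0% |
| 0.72 / 0.70 / 0.66 | 4.1% | 6.3% |
| 0.75 / 0.717 / 0.65 (linear) | 3.5% | 7.5% |
| 0.60 / 0.48 / 0.365 | 2.7% | 7.9% |
| 0.80 / 0.733 / 0.60 (linear) | 2.1% | 10.2% |
| 0.80 / 0.64 / 0.41 (AR(1)) | 0.8% | 12.3% |
| 0.95 / 0.90 / 0.80 (linear) | 0.4% | 14.9% |

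Week 16 stays close to nominal, at 4.1–4.8% in the three linear patterns. In terms of standard errors, the correct week-28 value exceeds the model's by about 5% in the mildest decay pattern and about 27% under AR(1) with 0.80. The correct week-10 value is about 4% and 26% smaller.

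**Check with dropout.** A simulation with 90 participants, 30% monotone dropout, AR(1) with 0.80 and 2,000 runs gave rejection rates of 1.4%, 6.4% and 13.2% at weeks 10, 16 and 28. The pattern survives the expected attrition.

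**Joint test.** In the same set of simulations, the 3-df likelihood ratio test of the whole interaction rejected in 5.3–7.5% of runs under decay, against 6.4% under constant correlation. The simulation standard error there is √(0.064 × 0.936/2000), about 0.55 percentage points. A second set, with 20,000 trials at 33 and 45 per arm, gave 5.7–7.1% under the linear patterns against 5.5–5.9% under equal correlation. The joint test hardly moves.

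**Group difference at one visit.** With complete data and equal variances, its standard error depends on σ² and n alone, so the correlation pattern does not enter.

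**The case against.** The strongest reply is that the protocol only says participant is a random effect. It does not say that nothing else will be modelled, and covariance structure is ordinary analysis-plan detail. That stands in part: the unseen plan may refine the structure, and its absence here is no fault. But the protocol does state a model, and it names less for the secondary outcomes than for the primary one. A random intercept is the natural reading of what is written.

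A second reply concerns the test. The stated likelihood ratio test may well drop the whole interaction, and that test is almost unaffected. This also stands. The wording, a parameter of interest together with reported beta coefficients, fits a single-coefficient test equally well, and the sizes in the table apply only to that use and to intervals for those coefficients.

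A reader might infer more: that the week-28 intervals are certainly too narrow, or that the false discovery rate step will rank miscalibrated p-values. The documents support neither. They give no correlations, and without decay there is no error. The false discovery rate consequence arises only if single coefficients supply the p-values; with one joint test per model there are no visit-specific p-values to rank.

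Finally, the calculation covers continuous outcomes with one value per visit. It does not carry over to the non-Gaussian GLMMs that the protocol allows, or to device and diary data with several values per block.

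**Conclusion.** The point holds as a conditional weakness in a stated method. If within-person correlation falls with time, the change-from-baseline coefficients are miscalibrated in opposite directions: true size about 6–15% at week 28 and 0.4–4% at week 10 for a nominal 5% single-coefficient test. This rests on the assumed correlations and on equal visit variances; unequal variances could alter the sizes. The top of the week-28 range comes from one very stable, weight-like pattern. The primary analysis is untouched. A change is worth making because the alternative contains equal correlation as a special case, so little is lost if no decay is present.

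**What to change.** For continuous secondary outcomes with one value per visit, state a repeated-measures model (MMRM) with group, visit and group-by-visit as fixed effects and an unstructured covariance over the four visits. Take the likelihood ratio or Wald test from that model. If it does not converge for an outcome, use a simpler structure in which correlation depends on time, or keep the random intercept with cluster-robust standard errors. In that last case Wald tests must replace the likelihood ratio tests, because robust standard errors leave likelihood ratio p-values unchanged.

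Copying the primary model's by-participant block term is not a remedy for these outcomes. With one Gaussian value per block it would need ten random-effect parameters plus a residual variance, eleven in all, where four visits identify only 4 × 5/2 = 10.

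The cost is a sentence in the analysis plan, a different R function, up to ten covariance parameters instead of two (with 63–68 completers expected from 90), and a slight loss of degrees of freedom. Outcomes with several values per block and non-Gaussian GLMMs keep their own models.

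### The likelihood ratio tests fixed for the secondary p-values are slightly liberal in the linear mixed models if referred to chi-square: about 5.3-5.5% against a stated 5%

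*Protocol article*

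**What the plan says.** All of the testing rules are in the protocol article, under Secondary outcomes analyses.

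- Level: "Statistical significance will be assessed using a two-sided alpha level of 0.05".
- Test: "p-values will be calculated using likelihood ratio tests comparing models with and without the parameter of interest".
- Model families: "Quantitative differences across assessment time points will be examined using GLMMs or linear mixed-effects models", chosen by the distribution of each outcome.
- Model terms: "Models will include group, assessment block, and group-by-assessment block interaction as fixed effects, with participant included as a random effect".
- Multiplicity: "A false discovery rate correction will be applied within each branch of secondary outcome analyses". The number of tests per branch is not given.

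Time points for analysis lists four occasions (weeks 4, 10, 16 and 28), so the full group-by-block interaction has 3 degrees of freedom. Sample size plans 90 participants, 45 per group, and says of the expected attrition: "This allows for approximately 63–68 participants to complete the study". Analysis population takes all randomised participants, and Handling of missing data relies on the mixed models to keep those with incomplete follow-up.

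Neither section on outcome analysis says whether the likelihood ratio statistic is referred to chi-square, F or a bootstrap distribution. The section on the primary outcome names no test.

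**The concern.** A likelihood ratio test of fixed effects compares two maximum-likelihood fits. Maximum likelihood divides by the number of observations rather than the residual degrees of freedom, so its variance estimates are too small. The chi-square reference also treats the variance as known. With 63 to 90 participants, both push p-values slightly below their correct values in a normal-theory mixed model.

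One test is barely affected. But the rule covers many secondary outcomes: sleep, circadian rhythm, mood, cognition, frailty, activity, body composition and vitamin D. The false discovery rate correction takes the p-values as valid, and the relative error is larger in the tail where its strictest thresholds lie.

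**Working it through.** **Inputs.** From the article: 90 randomised 1:1, attrition 25-30%, four visits, participant as the random effect, two-sided 0.05. Assumed: chi-square reference, normal outcome, complete balanced data, and a correct covariance model.

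**The plan's own figure.** 90 × 0.70 = 63 and 90 × 0.75 = 67.5, which gives the stated 63-68. I use n = 63 and 68, and n = 90 as the limit in which everyone contributes fully.

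**Random intercept, as worded for secondary outcomes.** With four balanced visits, the group-by-block tests lie wholly in the within-participant stratum. This has N = 3n contrasts and ν = 3(n − 2) residual degrees of freedom. For a test with q degrees of freedom,

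LR = N · log(1 + qF/ν), where F follows F(q, ν) under the null.

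Rejecting when LR exceeds the chi-square critical value c is the same as rejecting when F > (exp(c/N) − 1) · ν/q. The true size is that F tail probability.

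Example, n = 63 and q = 3: N = 189, ν = 183, c = 7.815. Then exp(7.815/189) − 1 = 0.04221, and F = 0.04221 × 183/3 = 2.575. P(F(3, 183) > 2.575) = 0.0554.

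| n | q | ν | F cut-off at 0.05 | true size at 0.05 | true size at 0.05/6 = 0.00833 |
|---|---|---|---|---|---|
| 63 | 1 | 183 | 3.758 | 5.41% | 0.00953 (+14%) |
| 63 | 2 | 183 | 2.947 | 5.50% | 0.00970 (+16%) |
| 63 | 3 | 183 | 2.575 | 5.54% | 0.00976 (+17%) |
| 68 | 1 | 198 | 3.764 | 5.38% | 0.00943 (+13%) |
| 68 | 2 | 198 | 2.951 | 5.46% | 0.00959 (+15%) |
| 68 | 3 | 198 | 2.577 | 5.50% | 0.00965 (+16%) |
| 90 | 1 | 264 | 3.783 | 5.28% | 0.00915 (+10%) |
| 90 | 2 | 264 | 2.962 | 5.34% | 0.00927 (+11%) |
| 90 | 3 | 264 | 2.584 | 5.37% | 0.00931 (+12%) |

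The threshold 0.05/6 is only an illustration. Six matches the number of cognitive tests listed under Cognition, and in a step-up procedure it applies to the smallest p-value alone.

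A simulation of the 3-df case with 20,000 runs gave 5.37% (n = 63), 5.72% (n = 68) and 5.48% (n = 90). Its Monte Carlo standard error is √(0.055 × 0.945/20,000) = 0.16 percentage points, so it agrees with the formula.

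**Participant-by-block effects, for comparison.** Here the p interaction contrasts have an unstructured covariance, and LR = n · log(1 + T²/(n − 2)), with T²(n − 1 − p)/((n − 2)p) following F(p, n − 1 − p). The size at 0.05 for p = 3 is 6.07% (n = 63), 5.99% (n = 68) and 5.73% (n = 90).

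**The case against.** The strongest objection is that the article never commits to a chi-square reference. A likelihood ratio statistic referred to a parametric bootstrap would meet its wording exactly, and the reference distribution is a detail that a separate analysis plan, promised before data analysis, would normally settle. This stands in part. The chi-square reference is an assumption, and the article does not misstate anything. But the article does fix the test by name, and Kenward-Roger or Satterthwaite tests on restricted maximum likelihood fits would replace that test rather than fill in a detail of it.

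A reader might also infer four stronger claims that the document does not support.

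- *Every p-value in the trial is affected.* The sentence sits under the secondary outcomes. The primary outcome section names no test, so extending the rule to it is inference.
- *The tests rest on 63-68 people.* That is the expected number of completers. The analysis keeps all 90 randomised with partial data, so the effective number lies between the two.
- *The true level is about 6%.* The 5.7-6.1% range needs participant-by-block random effects. These appear only in the primary model, which is Poisson or Gamma on daily data, where the normal-theory formula does not apply. The secondary wording reads naturally as a random intercept.
- *The error always favours significance.* This is shown for normal-theory models only. None of these figures carries over to the generalised mixed models that the article also allows.

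**Conclusion.** The point holds as a minor one. For the linear mixed models of secondary outcomes as worded, and given a chi-square reference, the group-by-block tests run at about 5.4-5.5% with 63-68 participants and 5.3-5.4% with 90, an excess of roughly 0.3 to 0.5 percentage points. At 0.0083 the relative excess is about 10-17%. These figures also assume normal outcomes, balanced complete data and a correct random-intercept structure. No trial conclusion is shown to change, and the size for generalised mixed models is not established. The change is worth making because a more accurate test for the linear models costs almost nothing. Priority is low.

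**What to change.** Keep the models, outcomes and alpha. For the linear mixed models, state that p-values and confidence intervals come from F or t tests with Kenward-Roger or Satterthwaite degrees of freedom on restricted maximum likelihood fits, in place of the likelihood ratio test. In the balanced case above, the F test on (q, ν) degrees of freedom is exact at 5%. The cost is one sentence, standard R functions and slightly larger p-values: a chi-square p-value of 0.050 on 3 df becomes 0.055 at n = 63.

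For the generalised mixed models the likelihood ratio test can stay. A parametric bootstrap of its statistic is an optional check, at the cost of computing time. Either way, the analysis plan should name the reference distribution and say which test applies to the primary outcome.

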#### Handling of missing data

Missing outcome data will be examined for patterns and assumed to be missing at random. Mixed-effects models inherently accommodate unbalanced repeated measures. For questionnaire outcomes, multiple imputations using chained equations will be considered. Sensitivity analyses (best-case/worst-case) will be conducted to assess robustness of findings. Missing or irregular data from the wearable light loggers will not be imputed. Irregular data may be regularized to a consistent time series within a participant and collection period. Participant days missing more than 2 h of data will be excluded from metric calculations and thus further analysis. Biller et al. (Malaysia/Switzerland) found that 6 h of missing data led to non-significant differences in a month-long data collection effort per participant [34]. As the follow-up period only contains 2 weeks of data collection, we choose this more conservative threshold.

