### Intervention

#### Experimental intervention

The experimental intervention is the LightUP mHealth smartphone application (app), which is downloaded onto participants’ own smartphones and used for 12 weeks, following a 4-week baseline monitoring phase. Participants in the intervention group will also wear a pendant-worn ActLumus light logger and a wrist-worn Garmin Vivosmart 5 activity tracker throughout the intervention period.

The LightUP app delivers evidence-based behaviour change techniques, including personalised feedback, self-monitoring, goal setting, and educational messages related to healthy light exposure. Participants are able to view their daily light exposure levels directly within the app, supporting self-monitoring and awareness of light-related behaviours. The app was co-designed with older adults and community service providers using a participatory, user-centred approach. The co-design process and development framework have been described in a previously published protocol paper [19].

Data from the ActLumus light logger are integrated into the app to tailor recommendations and to support participants in meeting daily and weekly light exposure targets. The app incorporates simple reward features, such as the awarding of trophies, to reinforce engagement and goal attainment. To support sustained engagement, participants receive a mid-intervention drop-in session during the intervention period.

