### Outcomes

#### Primary outcome

The primary outcome is the effectiveness of the LightUP app in improving light exposure behaviour in older adults. This will be assessed using data from the ActLumus wearable light logger (ActLumus, Condor Instruments; São Paolo, Brazil) across the 4-week baseline, the 12-week intervention and the 2-week follow-up monitoring period. The primary analysis metric is the mean daily time (minutes per day) above 250 lx melanopic equivalent daylight illuminance (melanopic EDI) during daytime hours. Changes will be calculated relative to baseline and both short-term effects (during the 12-week intervention) and longer-term effects (during follow-up) will be examined.

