### Statistical analysis

#### Analysis population

Analyses will follow the intention-to-treat principle, including all randomised participants in their assigned groups. A per-protocol sensitivity analysis will be performed including only participants with high adherence (≥ 80% app engagement and valid device wear).

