#### Primary outcome analysis

The primary endpoint is light exposure behaviour, operationalised as the mean daily time (minutes per day) spent above 250 lx melanopic EDI during daytime hours. Light exposure patterns will be analysed per individual using generalised linear mixed models (GLMMs). Daily TAT values will be entered into models including group assignment and assessment block/day-in-trial as fixed effects, with participant-level random effects to account for repeated daily measurements.

Based on prior analyses of TAT in a Malaysia–Switzerland light exposure study [34], Poisson and Gamma error distributions were identified as an appropriate fit for mixed-effects modelling and are therefore used for all analyses with TAT as the dependent variable.

The full model in Wilkinson notation will follow this specification:$$\begin{aligned}&\:\mathrm{Outcome\:variable}\:\sim\:\mathrm{group}*\mathrm{assessment\:block}\\&+\mathrm{sex}+\mathrm{age}+\left(\mathrm{assessment\:block}\right|\mathrm{participant})\:\end{aligned}$$

Model diagnostics will include visual checks for homoscedasticity, normality of residuals and random effects, and their location at zero. Baseline characteristics, including sociodemographic variables, health status, and baseline outcome measures, will be summarised descriptively by study group, and selected variables may be included as covariates in secondary or exploratory analyses where appropriate.

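### The 2 h rule for valid logger days is not tied to daytime and the printed model has no valid-time term, so arm differences in recorded daytime can enter the TAT250 contrast

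*Protocol article*

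**What the plan says.** Under Primary outcome the protocol article defines an absolute daily amount: "The primary analysis metric is the mean daily time (minutes per day) above 250 lx melanopic equivalent daylight illuminance (melanopic EDI) during daytime hours". Under Primary outcome analysis, "Daily TAT values will be entered into models including group assignment and assessment block/day-in-trial as fixed effects", with Poisson or Gamma errors. The full model printed there contains group by assessment block, sex, age and participant-level random effects. It has no offset, denominator or wear-time term.

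Under Handling of missing data, "Missing or irregular data from the wearable light loggers will not be imputed", and "Participant days missing more than 2 h of data will be excluded from metric calculations". The threshold is defended by a previous study in which 6 h of missing data made no significant difference in month-long recordings; 2 h was chosen as stricter because follow-up has only two weeks of recording.

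Device wear enters the analysis only through the per-protocol set, which requires high "app engagement and valid device wear"; valid wear is not defined further. Under Experimental intervention, the active app shows participants their own light levels, uses logger data for recommendations and targets, and has "simple reward features, such as the awarding of trophies, to reinforce engagement and goal attainment". The placebo app logs the same data without the behaviour change components.

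**The concern.** The metric looks only at daytime, but the rule that decides which days count does not. Two consequences follow from the text as written.

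- A day with, say, 1 h 59 min of daytime unrecorded passes the rule and contributes whatever minutes were captured. Lost daytime can leave the count unchanged or lower it, never raise it, and nothing in the printed model corrects for that.
- A day with complete daytime and more than 2 h lost at night is discarded, although its TAT250 is fully observed.

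If loss were alike in both arms, the cost would be some attenuation and some wasted days. In this trial the device that measures the endpoint also drives goals, feedback and trophies in one arm only. That gives the active arm a reason to wear and sync the logger differently, and the reason starts at randomisation. A resulting difference in recorded daytime does not cancel against baseline. It goes into the group by block term, which carries the treatment effect.

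**Working it through.** **Inputs from the protocol article.** Reference mean TAT250 of about 98 min/day, target effect of 20%, SD 0.2 and two-sided alpha 0.05 (Sample size); up to 2 h of missing data tolerated per day (Handling of missing data); 31 to 34 completers per group (Sample size).

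**Assumptions not in the documents.** Daytime of 12 h (range 10 to 14 h); lost time spread evenly over daytime; the size of any arm difference in recorded daytime. The article gives no wear data.

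**Step 1, the plan's own yardstick.** 0.20 × 98 = 19.6 min/day, which reproduces the stated figure of about 20.

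**Step 2, shift in TAT250 with no true light effect.** Shift = 98 × (arm difference in recorded daytime ÷ length of daytime). With 12 h, each hour is worth 98 ÷ 12 = 8.2 min.

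- 0.5 h/day: 98 × 0.5/12 = 4.1 min/day, 21% of 19.6
- 1 h/day: 98 × 1/12 = 8.2 min/day, 42%
- 2 h/day: 98 × 2/12 = 16.3 min/day, 83%

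The 2 h line is the ceiling for recognised gaps under even loss: every day in one arm short by the full 2 h of daytime, none in the other. Over the range of day lengths it is 98 × 2/14 = 14.0 to 98 × 2/10 = 19.6 min/day. Loss concentrated in bright hours would cost more per hour, and loss in dim hours less.

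**Step 3, what this does to a test.** As a rough guide, read the SD of 0.2 as the between-participant SD relative to the mean and compare two arms of 31. The standard error is 0.2 × √(2/31) = 0.0508.

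- 0.5 h: shift 0.0417, or 0.82 standard errors; false-positive rate 13.0% against a nominal 5%
- 1 h: shift 0.0833, or 1.64 standard errors; false-positive rate 37.5%

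This is a simple two-mean comparison, not the planned mixed model.

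**Step 4, would scaling by valid time settle it?** Only if lost time resembles recorded time. Evenly spread, recognised gaps are fully corrected. But suppose active participants shed 2 dim hours from a 12 h day. Their unscaled TAT250 is still correct at 98 min. Scaled, it becomes 98 × 12/10 = 117.6 min, a spurious gain of 19.6 min/day, the whole target.

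**The case against.** The article gives real safeguards. Both arms wear the same devices, have similar notification timing and get reminders. Data streams are watched for failed syncing and flat batteries. The 4-week baseline with a group by block term removes most of any stable wear difference. The threshold is deliberate and stricter than the 6 h it cites. There is a per-protocol sensitivity analysis, and best-case/worst-case analyses are planned. Non-wear detection and metric code are commonly left to an analysis plan, and one is announced.

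Much of this stands, and it limits the likely size. It does not remove the point. Equal devices and reminders equalise the opportunity to wear, not wear itself. A baseline comparison cannot absorb a difference that starts at randomisation. A non-significant effect of 6 h gaps in another study does not show absence of bias between randomised arms. The per-protocol set selects on behaviour after randomisation, and the article does not say that the best-case/worst-case analyses cover partly recorded days.

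Two stronger readings are tempting and are not supported. A reader might infer that non-wear is counted as low light. The article does not say so: non-wear may be set to missing and fall under the 2 h rule. What can be said is that the coding is not stated, and that non-wear which goes undetected would be read as low light, with no 2 h cap. A reader might also infer a bias in favour of the app. Better wear in the active arm would inflate the effect, but poorer wear would mask it, and the Limitations section names device fatigue without assigning it to an arm.

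**Conclusion.** The point holds as a weakness in a stated rule, not as a demonstrated bias. The article fixes an absolute min/day endpoint, a day-validity rule not tied to the daytime window of that endpoint, no imputation of logger gaps, and a model without a valid-time term. Together they let an arm difference in recorded daytime pass into the primary contrast in either direction.

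Plausible sizes cannot be read from the documents. Arm differences of 0.5 to 1 h/day would shift TAT250 by about 4 to 8 min/day. The figure of about 16 min/day (14 to 20 across the assumed day lengths) is a ceiling for recognised, evenly spread gaps, not an expectation. All of these rest on the assumed day length, evenly spread loss and an assumed arm difference. It would also go too far to call the unscaled endpoint an error that must be replaced by a rate: Step 4 shows that scaling can create a false effect as large as the target.

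**What to change.** In the analysis plan still to be finalised:

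- Define the daytime window and apply the 2 h limit to that window when deriving TAT250.
- Treat non-wear, identified by one rule applied blind to allocation in both arms, as missing under that limit. One option is a motionless logger while the activity tracker shows movement.
- Report valid daytime minutes by arm and assessment block alongside the primary result.
- Keep minutes per day as the primary estimand. Add a sensitivity analysis with log(valid daytime minutes) as an offset in a log-link model, converted back to min/day. State that it removes bias only if lost time resembles worn time, and that it can mislead if dim hours are selectively lost.

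The cost is modest: more processing code and one extra model, all from data already collected. Some days will be reclassified. Days with complete daytime and long night gaps come back in, and days with more than 2 h of daytime non-wear drop out.
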